### 2.3 Evidence for a light hypersensitivity in bipolar disorder

Since the 1980s, it has been hypothesized that photosensitivity to the non-visual effects of light could be the cause of the seasonal variation and circadian dysregulation seen in bipolar disorder populations. Disruption caused by hypersensitivity to light cues in bipolar disorder can lead to mood instability, disrupted sleep and ultimately episodes of hypomania, mania and/or depression (which themselves are characterised by circadian phase shifts (
Moon *et al.*, 2016)). Seasonal patterns in bipolar mood episodes provide clinical support for this theory, with hospital admission data showing trends for more mania-related admissions in spring/summer and more depression-related admissions in autumn/winter (
Geoffroy *et al.*, 2014). There is also an observed effect of seasonal changes in daily sunlight exposure on clinical outcomes such as suicide attempts (
Bauer *et al.*, 2021).

As both circadian and circannual rhythms are strongly influenced by light levels, a sensitivity to light within the photoreceptive pathway could be the cause of disruption to biological rhythms in bipolar disorder. Specifically, large changes in light levels - for example, rapid changes in photoperiod length at the spring and autumn equinoxes, or due to trans-meridian travel - may have a detrimental impact on circadian rhythms and bipolar disorder symptoms.

Experimentally, it has been shown that individuals with bipolar disorder exhibit greater light-induced phase delays (
Ritter *et al.*, 2021). Interventional studies in acute patient populations have also shown that blue-light blocking glasses may be effective in treating manic episodes (
Henriksen *et al.*, 2016;
Hester *et al.*, 2021).

Melatonin suppression studies are the most direct way to test the causal effects of light on melatonin synthesis (and by proxy, circadian response to light). Several early studies showed that people with bipolar disorder have greater suppression of melatonin by light (
Hallam *et al.*, 2009;
Lewy *et al.*, 1981;
Lewy *et al.*, 1985;
Nathan *et al.*, 1999), supporting a light hypersensitivity hypothesis. However, much of this research was conducted in small samples, and was conducted prior to the discovery of melanopsin in the late 1990s (thus missing a key piece of information regarding photoreceptive pathways). Several studies did not support a bipolar disorder light hypersensitivity (
Lam *et al.*, 1990;

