### 2.4 A potential mechanism of action for lithium

Lithium has been in clinical use for over 70 years and is acknowledged to be the most effective long-term treatment for bipolar disorder. In the UK, the National Institute for Health and Clinical Excellence recommends lithium as a first-line treatment for bipolar disorder. However, lithium has variable efficacy within the bipolar disorder population, with roughly one third of individuals having a ‘full’ response. Lithium has many reported actions – including modulation of monoamine neurotransmission (
Ferrier *et al.*, 2006), inhibition of glycogen synthase kinase-3 (
Klein & Melton, 1996), reducing the hyperexcitability of neurons and neuroprotection (
Mertens *et al.*, 2015) – but the precise mechanism of action in bipolar disorder remains an active area of research. Given the considerable etiological and clinical heterogeneity of bipolar disorder, it is possible that lithium has different modes of action within different patient subgroups.

Central to this protocol is convergent evidence suggesting that lithium may work (at least in a proportion of patients) by stabilising aberrant circadian rhythms of mood, cognition and rest/activity. Animal studies demonstrate that lithium reduces light-induced phase delays (
Duncan *et al.*, 1998) and that it modulates the pupillary response to light (
Seggie *et al.*, 1989). In humans, 5 days of lithium ingestion was shown to significantly decrease melatonin suppression in healthy volunteers, with no significant effect on nocturnal melatonin secretion overall (
Hallam *et al*. 2005). Additionally, human MRI research showing that lithium accumulates in the eye (
Smith *et al*., 2018). Taken together, it is plausible that lithium’s circadian-regulating effects occur via an action at the level of the retina to reduce light sensitivity and non-visual response to light. If lithium were to normalise aberrant retinal signalling in some way, this may also reduce bipolar-specific visual responses to light. Further, sustained lithium use might be neuroprotective, preventing or attenuating progressive structural retinal changes.

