## 3 Protocol

### 3.1 Study objectives

The primary research question is ‘Do people with bipolar disorder have a hypersensitivity to visual and non-visual effects of light, and does lithium attenuate this hypersensitivity?’. This protocol is organized into 3 parts (Part A, B and C) to answer this question. The main objectives of each of these parts are as follows:

**
*3.1.1 Part A objectives*
**

1. To assess whether people with bipolar disorder (relative to controls with no history of psychiatric disorder) exhibit greater non-visual responses to light stimuli assessed by the light-induced suppression of melatonin secretion.2. To assess whether these melatonin responses are less pronounced in those individuals with bipolar disorder who are being treated with lithium therapy (compared to individuals with bipolar disorder not taking lithium).

**
*3.1.2 Part B objectives*
**

1. To characterize the visual, cortical and pupillary responses of people with bipolar disorder (relative to controls with no history of disorder) using a combined electrophysiological and psychophysical study protocol.2. To assess whether aberrant visual and non-visual responses are less pronounced in those individuals with bipolar disorder who are being treated with lithium therapy (compared to individuals with bipolar disorder not taking lithium).

**
*3.1.3 Part C objectives*
**

1. To assess whether people with bipolar disorder (relative to controls with no history of psychiatric disorder) exhibit microstructural changes in the retina.2. To assess whether these changes are less pronounced in those individuals with bipolar disorder who are being treated with lithium therapy (compared to individuals with bipolar not taking lithium).

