### 3.6 Study population

**
*3.6.1 Sample size calculation*
**

This study will assess 180 participants:

*n*=60 with bipolar disorder and currently on lithium therapy
*n*=60 with bipolar disorder and not taking lithium
*n*=60 healthy controls with no history of mental illness and no first-degree family history of mental illness

The required sample size for this study is calculated from melatonin measures relevant to Part A. This sample size is sufficient for both Part B and Part C of the project (see below). Sex and gender differences were not taken into consideration in study design or sample size calculations because there is no conclusive evidence of sex or gender differences in the primary study outcome measures.

**3.6.1.1
Part A Sample Size Calculation
**

Our subjects of interest are BD patients versus controls, with the BD group sub-divided into two groups: one where BD subjects are on lithium therapy and another where BD subjects are not taking lithium. Based on previous reports of light-induced melatonin suppression in BD (
Hallam *et al.*, 2009) we expect a difference of approximately 40–50% (Cohen’s d effect size 0.5–0.6) between the BD lithium group and the BD non-lithium group. As such, for 80% power with an alpha of 5%, we will need 42 participants in each of the three groups. Allowing for incomplete data collection in up 30% of participants, this means that we will recruit 60 participants in each group.

**3.6.1.2
Part B Sample Size Calculation
**

With this sample size (N=180 participants across three groups), a two-sided between-subjects t-test at 80% power with an alpha level of 0.05 will be able to reliably detect an effect size of d=>0.52, equivalent to a difference of 0.52 of a standard deviation (i.e., medium effect size). Comparably, a between-subject ANOVA with three groups would be able to detect an effect size of f=>0.23. For a clinical study of this kind, this represents a very high level of sensitivity. As a minimum, it will allow us to provide a more definitive characterisation of the observed phenomena than previous studies in this field. As a comparison, studies with groups of 20 participants, which are common in the existing literature, are capable of detecting an effect of d=>0.9 (two groups) or f=>0.41 (three groups), which are large effect sizes.

**3.6.1.3
Part C Sample Size Calculation
**

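### The effect size behind the Part A sample is not shown to apply to lithium versus non-lithium, so the stated 80% power for that question is unsupported

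*Protocol article*

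**What the plan says.** Part A has two objectives (section 3.1.1). The first compares bipolar disorder with controls: "To assess whether people with bipolar disorder (relative to controls with no history of psychiatric disorder) exhibit greater non-visual responses to light stimuli". The second compares patients on and off lithium: "To assess whether these melatonin responses are less pronounced in those individuals with bipolar disorder who are being treated with lithium therapy".

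The sample size in section 3.6.1.1 is attached to the second. Its basis is introduced as "Based on previous reports of light-induced melatonin suppression in BD", with one 2009 report cited, and the expectation follows: "we expect a difference of approximately 40–50% (Cohen’s d effect size 0.5–0.6) between the BD lithium group and the BD non-lithium group". The conclusion is that "for 80% power with an alpha of 5%, we will need 42 participants in each of the three groups". An allowance of up to 30% incomplete data takes this to 60 per group. Section 3.6.1 says the size of the whole study comes from this Part A calculation. No Part A effect size is given for bipolar disorder versus controls.

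Two places in the introduction bear on the source:
- Section 2.3 cites the same 2009 report, with three others, for this statement: "Several early studies showed that people with bipolar disorder have greater suppression of melatonin by light".
- Section 2.4 gives the only human evidence on lithium and melatonin suppression, from a different study: "5 days of lithium ingestion was shown to significantly decrease melatonin suppression in healthy volunteers".

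**The concern.** One citation serves two contrasts. In section 2.3 it supports a difference between people with and without bipolar disorder. In section 3.6.1.1 it supplies the size of a difference between patients on and off lithium. No sentence connects them. A disease effect can stand in for a treatment effect only if the treatment moves the group mean by as much as the disease did, and objective 2 asks for less than that.

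Whether lithium attenuates the response is half of the primary research question in section 3.1. A reader told that this comparison has 80% power could take a null result as evidence against the proposed mechanism, when a partial effect was never likely to be detected.

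**Working it through.** **Inputs from section 3.6.1.1.** d=0.5 to 0.6; alpha 5%, with sidedness not stated for Part A (Part B states two-sided); power 80%; 42 per group; 30% loss.

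**Step 1: reproduce the stated size.**
- Normal approximation, two-sided: n = 2(1.960+0.842)²/d² = 15.70/d². At d=0.6 this is 43.6, so 44 per group (45 by t-test). At d=0.5 it is 62.8, so 63 (64 by t-test).
- One-sided t-test at d=0.55: 42 per group.
- Three-group ANOVA with the non-lithium group d away from two equal groups: f = d√2/3. At d=0.6, f=0.283 and n=41.1, so 42 per group.
- Loss allowance: 42/0.7 = 60, as stated.

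The figure of 42 is thus reached at the favourable end of the range or with a one-sided test. At d=0.5 none of these routes gives 80%: with 42 per group the power is 0.620 for the two-sided t-test, 0.735 one-sided, and 0.644 for the ANOVA (f=0.236).

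**Step 2: power for lithium versus non-lithium.** Two-sided t-test at 5%, noncentrality d√(n/2), 2n−2 degrees of freedom. The half-size rows assume that d=0.5 to 0.6 is the bipolar excess and that lithium removes half of it, so d = 0.5×0.5 = 0.25 to 0.5×0.6 = 0.30.

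| d | Power, 42 per group | Power, 60 per group |
|---|---|---|
| 0.50 | 0.620 | 0.775 |
| 0.60 | 0.776 | 0.903 |
| 0.25 | 0.205 | 0.274 |
| 0.30 | 0.274 | 0.371 |

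For 80% power in the half-size case, 253 per group would be needed at d=0.25 and 176 at d=0.30.

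**Step 3: what the fixed sample can detect.** Solving the same t-test for d at 80% power gives 0.619 with 42 evaluable per group and 0.516 with 60. The second agrees with the 0.52 that section 3.6.1.2 gives for Part B.

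**Step 4: the two uses of the source.** Section 2.3 takes from the report a direction of effect in people with bipolar disorder. It gives no effect size and no lithium status. Section 3.6.1.1 takes from it a size for the on-versus-off-lithium difference. Section 2.4 cannot bridge them, because its lithium data come from another study, in people without bipolar disorder.

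**The case against.** The strongest reply is that the 2009 report is not at hand and may contain data on patients with and without lithium. Section 2.3 cites it in a group of four for one summary sentence and does not describe its arms. A reader might infer that the calculation uses the wrong comparator and that d=0.5 to 0.6 belongs to unmedicated or non-lithium patients versus controls. The document does not support either conclusion. It shows an effect size with an unexplained basis, not a proven misattribution.

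Other points on that side also have force:
- Full normalisation is within the stated ideas. Section 2.4 raises the possibility that lithium normalises retinal signalling, and the Conclusion speaks of correcting altered responses. In that case the two effects coincide on average.
- Lithium's effect need not be a share of the bipolar excess, since section 2.4 reports reduced suppression in healthy volunteers. The half-removal scenario is an illustration, not a prediction.
- Section 2.4 says that "lithium has variable efficacy within the bipolar disorder population, with roughly one third of individuals having a ‘full’ response". A reader might take one third as the expected attenuation, but the figure is a rate of clinical response and says nothing about how much melatonin suppression is removed.
- Using 42 per group assumes the full 30% loss. With all 60 evaluable, d=0.5 to 0.6 gives 78% to 90%.

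A journal article may leave detail to the full protocol. Here, though, the effect, its source and the contrast are all stated, and the difficulty lies in how they fit together. None of these replies supplies the missing link or makes 42 per group give 80% across the stated range.

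**Conclusion.** The point holds in a limited form. The article assigns d=0.5 to 0.6 to lithium versus non-lithium on the strength of a report it otherwise cites only for bipolar disorder, with no stated assumption joining the two. The 80% power claim is therefore not supported for the lithium question.

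Two sizes should be kept apart. At the stated effect, taken at face value, two-sided power with 42 per group is 62% to 78%; this needs no assumption beyond a two-sided 5% t-test. If the effect is instead the bipolar excess and lithium removes half of it, power is 21% to 27% with 42 per group and 27% to 37% with 60; this rests on an assumed share that the document does not give. No corrected sample size follows, because the document contains no separate effect size for the lithium contrast.

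**What to change.** In section 3.6.1.1:
1. State which contrast in the cited report yields d=0.5 to 0.6. If it is bipolar disorder versus controls, attach it to objective 1 and state the attenuation assumed for lithium versus non-lithium.
2. Replace the 80% claim for lithium versus non-lithium with what the fixed sample can detect at 80% power, two-sided 5%: d=0.62 with 42 evaluable per group and d=0.52 with 60.
3. Say that a null lithium contrast does not exclude a smaller, partial attenuation, and give the half-removal figures as an illustration labelled as an assumption.

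The cost is a few sentences and a less favourable power statement for the lithium question. Recruitment stays at 60 per group, and the change can be made while the study is recruiting.

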### 3.11 Statistical analysis

**
*3.11.1 Proposed analyses*
**

**3.11.1.1
Part A analyses
**

We will compute the area under the curve for the melatonin profile using the trapezoidal method and also compute the percentage difference between the healthy control group and the BD lithium therapy group, as well as between the healthy control group and the BD non-lithium treatment group. We will then use one-way ANOVA (or Kruskal-Wallis) with post-hoc analyses (Tukey) across the three groups, as well as undertaking general linear model analyses controlling for potential confounding variables such as age, sex, ethnicity, educational attainment, employment status, socioeconomic status, smoking status, alcohol use, sleep quality, chronotype, psychiatric history, medication use and score on the Alda lithium response scale. 

**3.11.1.2
Part B analyses
**

Statistical analyses for the various measures (pupillary response, colour perception, spatiochromatic processing, visual evoked potentials) across the three groups will be performed using linear mixed effect models with healthy control group set as the baseline (i.e., zero) level for all the comparisons. Models will also be evaluated for the contribution of confounding factors, including age, sex, ethnicity, educational attainment, employment status, socioeconomic status, smoking status, alcohol use, sleep quality, chronotype, psychiatric history and medication use and score on the Alda lithium response scale.

**3.11.1.3
Part C analyses
**

We will test the hypothesis that people with BD have significant differences in structural and functional measures of the retina and in the trajectory of change compared to controls. Additionally, we will assess whether individuals with BD who are taking lithium have an attenuated trajectory of change compared to those with BD on other medications. Student’s t-test and generalised estimation equations will be used to examine differences in retinal measures and psychophysical thresholds between the three participant groups. Spearman’s rank correlation coefficient will be used to investigate associations of retinal measures and psychophysical thresholds with other key parameters from the study data, including confounding demographic and clinical factors. Trajectory analysis will be used to assess changes in retinal parameters and psychophysical thresholds over time and how effective this approach is at stratifying participants.

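### Part A: 42 evaluable per group does not give 80% power across the stated d of 0.5–0.6 for the planned lithium versus non-lithium comparison (62–78% two-sided, 47–65% with Tukey)

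*Protocol article*

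**What the plan says.** Section 3.6.1.1 of the Protocol article gives the planning effect as a range: "we expect a difference of approximately 40–50% (Cohen’s d effect size 0.5–0.6) between the BD lithium group and the BD non-lithium group". It continues: "As such, for 80% power with an alpha of 5%, we will need 42 participants in each of the three groups". It does not name the test, say whether the 5% is one- or two-sided, or say which d in the range produced 42. The recruitment target follows: "Allowing for incomplete data collection in up 30% of participants, this means that we will recruit 60 participants in each group". The opening of 3.6.1 says that the study's required sample size comes from the Part A melatonin measures, so the other parts inherit it.

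Section 3.11.1.1 plans the Part A analysis: "We will then use one-way ANOVA (or Kruskal-Wallis) with post-hoc analyses (Tukey) across the three groups". Adjusted general linear models are also planned.

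Section 3.6.1.2, on Part B, is more explicit. It starts "With this sample size (N=180 participants across three groups), a two-sided between-subjects t-test at 80% power" and gives a smallest detectable d of 0.52. For the omnibus test it says that "a between-subject ANOVA with three groups would be able to detect an effect size of f=>0.23".

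**The concern.** The effect range, power, alpha and group size in 3.6.1.1 do not fit together for the contrast to which the effect size is attached. The mismatch shows inside 3.6.1 without any calculation. Part B says that 60 per group, with a two-sided t-test at 80% power, detects d of 0.52 or more. Part A says that 42 per group is enough for a range that begins at 0.5.

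Whether lithium attenuates light hypersensitivity is half of the primary research question in 3.1. If the lithium contrast comes out null, readers will judge it against a claimed 80% power. If the real figure is between one half and three quarters, they are likely to take the null as stronger evidence of no effect than it is.

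**Working it through.** **Inputs.** d = 0.5–0.6, power 80%, alpha 5%, 42 evaluable per group, up to 30% incomplete data, 60 recruited per group (all 3.6.1.1). ANOVA or Kruskal-Wallis with Tukey, three groups (3.11.1.1). Part B: 60 per group, two-sided t-test, alpha 0.05, detectable d 0.52 and f 0.23 (3.6.1.2).

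**1. What reproduces.**
- Inflation for loss: 42 / (1 − 0.30) = 60.
- Part B at 60 per group: detectable d = 0.516 and f = 0.233. Both stated values are right for all 180.
- The figure 42 from a one-sided 5% t-test at d=0.55: 41.6, rounded up to 42 (power 80.4%).
- The figure 42 from an omnibus one-way ANOVA with one group 0.6 SD from two equal groups: f = 0.6 × √2/3 = 0.283, giving 41.2, rounded up to 42 (power 80.9%).

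**2. Number needed for a two-sided pairwise comparison.** Normal approximation: n per group = 2(1.960 + 0.842)² / d².
- d=0.5: 15.70 / 0.25 = 62.8, so 63. The exact noncentral-t answer is 64.
- d=0.55: 15.70 / 0.3025 = 51.9, so 52. Exact: 53.
- d=0.6: 15.70 / 0.36 = 43.6, so 44. Exact: 45.

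**3. Power with 42 per group.** The noncentrality is d × √(42/2) = 4.583d, that is 2.29, 2.52 and 2.75. The two-sided t critical value on 82 df is 1.989. The Tukey critical value for three groups on 3 × 41 = 123 df, on the t scale, is 2.372.

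| d | Two-sided t-test | Tukey pairwise | One-sided t-test |
|---|---|---|---|
| 0.50 | 62.0% | 47.0% | 73.5% |
| 0.55 | 70.2% | 56.0% | 80.4% |
| 0.60 | 77.6% | 64.7% | 86.0% |

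With 42 per group, 80% power is reached at d = 0.62 (two-sided t-test) or d = 0.70 (Tukey).

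**4. No loss at all.** With 60 evaluable per group, the two-sided t-test has 77.5% power at d=0.5 and 90.3% at d=0.6. Tukey has 64.6% and 82.1%. Even full retention does not reach 80% at the lower end of the range, which agrees with Part B's own 0.52.

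**5. Part B, if loss also reached 30%.** With 42 evaluable per group, detectable d = 0.62 and f = 0.28. This is a sensitivity figure only, because the document gives no loss rate for Part B.

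**The case against.** Part A names neither test nor sidedness, so a flat statement that 42 does not give 80% power assumes a test. As step 1 shows, 42 has two plausible origins. The ANOVA route deserves weight: 3.6.1.1 opens with bipolar patients versus controls and sizes three groups, and 3.11.1.1 makes one-way ANOVA the first Part A test. Nor is 81% the most that the omnibus test could offer. If lithium only partly attenuates the response and controls lie 0.2 SD below the lithium group (an assumed offset), omnibus power at 126 is 93% for d=0.6 and 84% for d=0.5.

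This shows that the sponsor may have made no slip of arithmetic. It does not rescue the sentence. The effect size is attached to lithium versus non-lithium, and a significant omnibus F does not establish that contrast. A one-sided test does not match a plan built on ANOVA, Kruskal-Wallis and Tukey, nor Part B's two-sided test, and it still gives only 73% at d=0.5.

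It is also fair that the gap is small at the top of the range (77.6% against 80% at d=0.6) and that 30% is a worst case. With 25% loss, 45 per group remain and d=0.6 has 80.4%. The shortfall at d=0.5 stays under every pairwise reading at 42 per group.

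A reader might infer that Part B's sensitivity is misstated because it ignores the 30% loss. The document does not support that. Part B states its basis as all 180 participants, its figures are correct on that basis, and the 30% appears only under Part A, which involves overnight stays and serial blood sampling.

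**Conclusion.** The point stands in a bounded form. For the lithium versus non-lithium contrast, tested non-directionally with 42 evaluable per group, power is 62–78% over d = 0.5–0.6 with a two-sided t-test and 47–65% with Tukey. The stated 80% applies at d = 0.62, just outside the range.

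These figures assume equal groups, normal outcomes with a common SD, and loss at the full 30%. They take no account of any precision gained from the planned covariate-adjusted models.

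Two stronger readings are not supported. One is that 42 cannot be derived at all: it can, under tests that Part A neither states nor plans for this contrast. The other is that Part B contains an error: applying 30% loss there is an assumption, and it gives a range of 0.52 to 0.62 for d and 0.23 to 0.28 for f.

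**What to change.** Keep 60 per group. In 3.6.1.1, name the test, the sidedness and the single d from which 42 was obtained, and replace the power statement with wording such as: 42 evaluable per group gives 80% power for d = 0.62 (two-sided, single contrast) and 62–78% for d = 0.5–0.6; 47–65% if the contrast is tested by Tukey.

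Optionally, add to 3.6.1.2 that the detectable effects of 0.52 and 0.23 assume all 180 evaluable and would become 0.62 and 0.28 if Part B loss also reached 30%.

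Taking the lithium contrast out of the Tukey family, or adjusting for the first-night melatonin baseline, could recover power. Both are design choices for the sponsor and are not needed for this correction.

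The cost is a few sentences and a less favourable stated power. No participants, visits or procedures change. The article reports the study as still recruiting, so the statement can be corrected before analysis.
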